## Exclusion Criteria

Participants who cannot comprehend and speak fluent English will be excluded from participation. Similarly, participants will be excluded if they score ≥20 on the Center for Epidemiologic Studies Depression Scale (CESD), a measure of recent depressed feelings and behaviours, and/or scoring two or more standard deviations below the mean for age, gender, and education on the Paired Associate Learning (PAL), a measure of memory ability. Participants who are concerned about participating due to a health condition will be advised to consult their GP about their fitness and ability to participate: this also encompasses any participants with a probable severe mental health condition (as assessed by a brief telephone screening questionnaire). Volunteers with very high blood pressure (i.e. >180mmHg/>110) identified during the first heath assessment session will be advised to consult their GP as soon as possible; and discuss the potential benefit of taking part in this study. Volunteers who are concerned about participating due to a health condition will be advised to consult their GP about their fitness and ability to participate, and those advised not to participate will be excluded. Sampling

We will attempt to include participants who vary on the following criteria: retirement status; chronological age (younger vs older); gender; work category (manual, semiskilled or technical, managerial or professional), and work-related activity (physically demanding or sedentary). We will weight recruitment in favour of blue collar, manual and lower managerial occupations. To facilitate recruitment across these categories we will attempt to recruit employers who provide different forms of employment within the business (e.g. both office and blue collar positions), and if necessary, recruit employers that employ people in particular occupations if these are under-represented in our sample (e.g. high in work-related physical activity).

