# STUDY Procedure

This pilot trial will work through the following steps:

1. The trial administrator and (where appropriate) collaborating Health Improvement Specialists will contact Human Resources departments of local businesses to ask them if they would be willing to advertise the study to their employees or constituents (email, letters, posters in workplace etc) and where appropriate, contact individual employees or members of the organisation directly (e.g. personalised e-mail). If recruitment is also conducted in the community (e.g. in order to recruit people who have retired) then we will also contact community organisations of older adults and display posters in locations that may be frequented by people living in low socio economic neighbourhoods (more likely to have retired from blue collar or manual occupations rather than managerial or professional roles), and which aren’t linked specifically to existing membership or engagement with routine physical activity (e.g. sports centres). Our strategy therefore will be to display posters in low SES wards in Newcastle (e.g. Benwell, Elswick ) in the following locations: pubs; working men’s clubs; libraries; Citizen Advice Bureaus; supermarkets; noticeboards in religious buildings (e.g. churches, mosques) and shop windows.
2. Potential participants who are interested in participating will be asked to make contact with the trial administrator or to agree for the Human Resources department or community organisation to pass on their details to the research team who will then contact the potential participant directly.
3. The trial administrator will contact the Human Resources departments and community organisations in one week if there has not been any contact.
4. Over the telephone, a member of the research team will assess the potential participants for eligibility using the defined inclusion and exclusion criteria.
5. Eligible participants will be emailed or sent a study invitation letter, a participant information sheet and a consent form. They will be informed that one of the study team will make contact with them in the next five working days to discuss their participation in the study and to answer any questions.

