6. In the next five days, the trial administrator will telephone each eligible participant to answer any questions and to ascertain whether they would like to accept the invitation to participate. If there are any questions that can’t be answered over the phone by the administrator, a date for follow-up correspondence (either by e-mail or phone according to the preference of the potential participant) will be made. The administrator will request an answer to the question from the relevant trial team personnel, and will then relay this information to the participant during the arranged follow-up correspondence. On verbal consent, the trial administrator will ask that the participant sign the consent form and keep it until one of the research team visits them. The administrator will then schedule an appointment at a convenient time when one of the study team will visit the participant at their home or place of work to obtain the signed informed consent form and conduct the baseline assessment. The researcher will attend the appointment with spare consent forms in case the participant mislaid their original consent form.
7. Baseline assessment visit - after receiving informed consent, a member of the study team will administer the HAP battery assessment as per protocol (Appendix A). The activity monitor device will be attached to the participant, and it will be explained that the device is to be worn continuously for the next 7 days. The participant will be provided with a prepaid stamped address envelope to return the device after 7 days. The 24 hour recall dietary assessment tool procedure will be explained and participant will complete the first of three days to be recorded, and a web link to the social relationships tools will be provided. During this assessment session participants will be asked to provide information on smoking, alcohol consumption and demographic (Attachment 4 – Baseline data form).
8. The trial administrator will be informed by the member of the study team when baseline assessment is complete and the administrator will randomise the participant to one of the trial conditions recording key information (e.g. name, D.O.B. and assigned identification number) into a central database. A pedometer and instructions for its use will be posted to participants allocated to receive the LEAP intervention. The trial administrator will telephone or email the participant a few days later to check that the pedometer was received.

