a) Executive function. Verbal and category fluency tests will be used to assess participants’ executive function. Within a set timeframe, usually one minute per letter participants are instructed by the experimenter to speak aloud as many words as possible that begin with a specific letter (phonemic fluency) – this is repeated 3 times for 3 different letters (e.g., CFL or PRW). In a separate one minute window, participants are then instructed to speak aloud as many words as possible which belong to a specific category, such as animals (category fluency). Participants will be audio-recorded when performing these tasks, to allow for detailed analyses of the responses made, including total number of words, repetition and errors. Completion of these tests takes approximately 5 to 7 minutes.

b) Episodic memory. The paired associates learning (PAL) CANTAB test will be used. Boxes are displayed on a touchpad screen. The participant watches as the boxes are ‘opened’ automatically, one by one, in a randomised order. One or more of them will contain a pattern. The patterns are then displayed in the middle of the screen, one at a time, and the participant must touch the box where the pattern was originally located. If the participant makes an error, the patterns are re-presented to remind the participant of their locations. The difficulty level increases through the test. The number of patterns increases from one (with 7 empty boxes) to eight (with no empty boxes), which challenges even very able participants.

Test administration takes approximately 10 minutes, depending on level attained. The PAL has 21 outcome variables including errors made by the participant, the number of trials required to locate the pattern(s) correctly, memory scores and stages completed. These data are produced automatically.

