c) Quality of life. The control, autonomy, pleasure and self-realization, quality of life scale (CASP-19) will be used to assess participants’ multidimensional quality of life. This tool is administered via the NIH Assessment Center website. The test consists of 19 items relating to four theoretically-derived domains: Control (4 items), Autonomy (5 items), Pleasure (5 items), Self-realisation (5 items). Participants report the frequency with which they experience certain feelings or cognitions using a four-point Likert scale ranging from “Often” to “Never.” Items are scored automatically via the Assessment Center (with reverse coding of positive responses, so that higher scores equal higher QoL. The authors define the scale ranges as 0 (complete absence of QoL) to 57 (total satisfaction in all four domains). Administration of the test takes ~ 5 minutes

d) Mental health. The centre for epidemiological studies depression scale (CES-D) will be used to assess participants’ mental health, with a specific focus on depressive symptomatology. This test is administered via the NIH Assessment Centre. Participants are prompted to respond to 20 items by indicating the frequency with which they have experienced depressed mood, feelings of guilt, worthlessness and helplessness, psychomotor retardation, loss of appetite and sleep difficulties over the previous 7 days. Responses range from often (5 or more days out of 7) to not at all (one or zero days). Completion of the test takes approximately 5 minutes and the score is calculated automatically by the NIH Assessment Center.

5. Social Wellbeing (Gershon et al., 2010, Salsman et al., 2013)

We intend to use the following measurement tools, all of which will be administered via the National Institute of Health (NIH) Assessment Centre though a computer or smartphone and internet connection. The instruments can also be administered in paper and pencil format as short form instruments (typically from six to 14 items), although an inclusion criteria to the trial is that participants have access to the internet.

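### Step 4 settles eligibility by telephone, but the PAL exclusion cannot be scored in a call, the CES-D appears only in the baseline battery, and no visible step checks either score before randomisation

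*Protocol*

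**What the plan says.** **The exclusions.** The Protocol's Exclusion Criteria contain two rules based on test scores. One concerns depressive symptoms: "participants will be excluded if they score ≥20 on the Center for Epidemiologic Studies Depression Scale (CESD". The other concerns memory: "scoring two or more standard deviations below the mean for age, gender, and education on the Paired Associate Learning (PAL".

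**When eligibility is decided.** STUDY Procedure, step 4: "Over the telephone, a member of the research team will assess the potential participants for eligibility using the defined inclusion and exclusion criteria". Step 5 treats the matter as settled: "Eligible participants will be emailed or sent a study invitation letter, a participant information sheet and a consent form".

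**When the tests are given.** Both belong to the HAP battery in Appendix A, which step 7 places at the baseline visit after consent.
- Appendix A, Cognitive Function, item b: "The paired associates learning (PAL) CANTAB test will be used. Boxes are displayed on a touchpad screen". The CANTAB tablet is on the equipment list for the assessment.
- Appendix A, Psychological Wellbeing, item d, on the CES-D: "This test is administered via the NIH Assessment Centre".

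**What triggers randomisation.** Under step 8 the administrator is told "when baseline assessment is complete and the administrator will randomise the participant to one of the trial conditions". The step mentions no score.

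**What the pilot must deliver.** The section on scientific rationale lists the number of eligible people among the facts needed before a definitive trial. The first question under Recruitment and retention uses eligible people as the base of the recruitment rate.

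**The concern.** An exclusion criterion needs a point in the procedure at which it is applied. For these two, the written sequence gives none that works. The telephone stage comes before the tests, and the stage after the tests goes directly to randomisation.

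Two things are at stake. First, someone who meets a stated exclusion could be randomised by staff who follow every step correctly. Secondly, the count of eligible people would include some who are not eligible. Anyone removed informally at baseline would have no defined place in the participant counts. A definitive trial planned from those counts would allow for too few baseline visits.

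**Working it through.** **1. The plan's own figure.** The total of 90 at 2:1 gives 90 × 2/3 = 60 LEAP and 90 × 1/3 = 30 control, as stated. It is a feasibility number with no power calculation behind it, and nothing below depends on power.

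**2. The sequence, side by side.**

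| Step | Action | PAL score available? | CES-D score available? |
|---|---|---|---|
| 4 | Telephone eligibility on the defined criteria | No, touch-screen test | Not as described |
| 5–6 | Eligible people invited; acceptance obtained | No | Not as described |
| 7 | Consent received, then HAP battery | Yes | Yes |
| 8 | Randomise when baseline is reported finished | Yes, but no check stated | Yes, but no check stated |

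The only telephone instrument mentioned is for a "probable severe mental health condition (as assessed by a brief telephone screening questionnaire". It is not named as the CES-D, and it leads to GP advice. The Exclusion Criteria state an action for one finding at the first session, very high blood pressure, and that too is GP advice. No action is stated there for a PAL or CES-D score found at baseline.

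**3. Size for PAL alone.** Assume scores are normal and these volunteers resemble the norm population.
- Proportion at least 2 SD below the norm: Φ(−2) = 0.0228.
- Expected among 90: 90 × 0.0228 = 2.0.
- Chance of at least one: 1 − (1 − 0.0228)^90 = 0.87.

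**4. Size with the CES-D added.** The documents give no proportion scoring 20 or more. Let c be that proportion among people who pass the telephone stage, assumed to be 5% to 15% and independent of PAL. The proportion meeting either exclusion is f = 1 − (1 − 0.0228)(1 − c).

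| Assumed c | f | Expected of 90 (90f) | Baseline visits to randomise 90 within the criteria, 90/(1 − f), rounded up |
|---|---|---|---|
| 5% | 7.2% | 6.4 | 97 |
| 10% | 12.0% | 10.8 | 103 |
| 15% | 16.9% | 15.2 | 109 |

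If instead everyone who failed PAL also failed the CES-D, f would equal c and the expected numbers would be 4.5, 9.0 and 13.5. The assumed c drives the result far more than the independence assumption.

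**5. Effect on the feasibility outputs.** Let E people pass the telephone stage, and let a proportion a accept whether or not they are excludable.
- The acceptance rate is aE/E = a, and among the truly eligible it is a(1 − f)E/[(1 − f)E] = a. It does not change.
- The count of eligible people does change: E is reported where (1 − f)E is correct.
- Visits are affected as well. On the assumptions above, 7 to 19 extra baseline visits (97 − 90 to 109 − 90) would be needed, at up to about 2 hours each by the Protocol's estimate, or 14 to 38 hours.

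**The case against.** The strongest reply is that the Protocol does not intend to randomise ineligible people. Its Randomisation section says that it is eligible participants who are assigned, the Exclusion Criteria say that people beyond the cut-offs are excluded, and baseline comes before randomisation. Both scores are produced automatically, so they can be available in time. On this view step 4 is a first screen and step 8 an administrative trigger.

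Much of that stands. A reader might infer that the plan provides for randomising ineligible people. The documents do not support that: the steps permit it by omission, against the plan's stated intent. The reply still does not supply the missing check, because in steps 5 and 6 the word eligible already means having passed the telephone call.

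Other limits also stand.
- **Missing material.** Figures 1 and 2, the HAP administration guidelines and the baseline data form are not in the available text, and any of them could contain a check. Step 4 would still conflict with the description of PAL.
- **CES-D.** A questionnaire of 20 items could be read out by telephone, although the Protocol describes no such use. The impossibility is firm for PAL only.
- **Web link.** A reader might infer that the CES-D is completed after the visit through the web link, since one Appendix A sentence gives a joint completion time for the psychological and social instruments. Step 7 and Appendix A tie that link to the social relationships tools, so late completion is not shown.
- **Recruitment rate.** Acceptance precedes the battery and decliners never have scores, so a fully eligible denominator cannot be observed. The acceptance percentage need not be biased.

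**Conclusion.** The contradiction holds. Step 4 cannot be carried out as written for PAL, the CES-D is described only after consent, and no visible step applies either cut-off before randomisation. The consequence is a gap through which people who meet an exclusion can be randomised, together with an overstated count of eligible people. It is not evidence that the plan means to admit them, nor that the acceptance rate is wrong.

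The size cannot be fixed from the documents. About 2 of 90 for PAL rests on normality and on volunteers who match the norm. About 6 to 15 of 90 for the two together also rests on an assumed 5% to 15% at or above the CES-D cut-off and on independence. The contradiction does not depend on these figures.

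This should be fixed. It is not more serious than that: the trial is a pilot not powered to detect change, the Protocol describes the intervention's risks as minimal, and the correction is a matter of wording.

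**What to change.** Reconcile the Exclusion Criteria with STUDY Procedure steps 4, 7 and 8, leaving both cut-offs as they are:

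1. Limit step 4 to the criteria that can be asked by telephone.
2. State that the CES-D and PAL are completed and scored at the baseline visit. Name which of PAL's 21 outcome variables the criterion uses, so that the check can be carried out.
3. Insert a step between 7 and 8 in which the assessor confirms that neither score meets its exclusion before the administrator may randomise.
4. Report four counts separately: telephone-eligible, accepted, excluded at baseline on CES-D or PAL, and randomised.
5. Keep telephone-eligible people as the base of the acceptance rate, because decliners have no scores. Use the baseline screen-failure rate when projecting visits for the definitive trial.

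The cost is a few sentences and one tick-box on the baseline form, with no added test, staff or type of visit. If the target of 90 randomised is kept, each person excluded at baseline has to be replaced by another baseline visit, and the reported number eligible will be somewhat lower.

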# Outcome Assessment

## Assessment Times

- Baseline before randomisation
- 2 months after starting the intervention.

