## Baseline and 2-month Follow-up Assessments

The assessments at baseline and at 2-months are identical. The assessments will include behavioural measures of physical activity and inactivity, dietary intake and social relationships, and HAP measures. It is estimated that these measurements can be completed within 2 hours. The assessments will take place at the participant’s place of work. Participants who have retired will be asked to attend assessments at their previous place of work, at a local privately hired venue (e.g. community hall), or in their own homes. Assessments will be carried out by a member of the study team trained to administer the various measures. The psychological and social wellbeing questionnaires will be self-reported by the participant. In Appendix A there is the measurement battery protocol, including the list of measures, instructions for their administration and analysis of the data acquired).

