9. Seven days after the trial administrator has confirmed that participants allocated to the LEAP intervention have received the pedometer, the trial administrator will email them a web link to access the intervention. They will also be provided with contact details of members of the study team to troubleshoot technical problems.
10. Immediately after the baseline assessment, the trial administrator will email a web link to the NHS LiveWell resource to participants allocated to receive the control intervention.
11. All participants will be reminded that they will be contacted again in approximately 6 weeks to arrange a follow-up visit by a member of the study team in two months’ time.
12. In the next three days, the trial administrator will telephone or email the participant to check that they received the web link to the intervention. During the call the administrator will arrange a date and time for a qualitative interview with those participants who have been identified as suitable using the purposive sampling procedure described in the qualitative protocol (see section 9). For participants randomised to the intervention group, the interview will be scheduled to take place no sooner than a week following the call to allow the participant to use the LEAP intervention and to ensure the interview is not conflated with use of LEAP. Approximately (n=6-8) appointments will be made with participants in the LEAP arm, and up to 4 appointments with participants in the control, with a further 6-8 and 4 appointments respectively being made toward the end of the trial. This will allow the research team to compare accounts of participation at the start and end of the trial respectively, potentially identifying unexpected participant expectations or disappointments/misunderstandings throughout the trial.
13. Six weeks after receiving the link to the LEAP or control intervention, the trial administrator will telephone participants to schedule an appointment at a convenient time in the next two weeks when one of the study team will visit the participant at their home or place of work to conduct the follow-up assessment. During the call the administrator will arrange a date and time for a qualitative interview with participants (n=6-8 in LEAP; n= 4 in control) who have been identified as suitable for a qualitative interview.

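### The trigger for randomisation and release of material is tied to the baseline visit, although activity, diet and possibly social baseline data are still being collected

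*Protocol*

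**What the plan says.** The Assessment Times section places the first assessment as "Baseline before randomisation". The next section defines its content: "The assessments will include behavioural measures of physical activity and inactivity, dietary intake and social relationships, and HAP measures". It adds: "It is estimated that these measurements can be completed within 2 hours".

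STUDY Procedure then gives the order of events.

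- **Step 6** books an appointment at which a team member visits to take consent and carry out the baseline assessment.
- **Step 7** has the activity monitor attached at that visit, and "it will be explained that the device is to be worn continuously for the next 7 days"; the participant posts it back afterwards. For diet and social measures, "participant will complete the first of three days to be recorded, and a web link to the social relationships tools will be provided".
- **Step 8** has the visiting team member tell the administrator "when baseline assessment is complete and the administrator will randomise the participant to one of the trial conditions". It continues: "A pedometer and instructions for its use will be posted to participants allocated to receive the LEAP intervention".
- **Step 9** sends the LEAP web link seven days after receipt of the pedometer is confirmed.
- **Step 10** covers controls: "Immediately after the baseline assessment, the trial administrator will email a web link to the NHS LiveWell resource to participants allocated" to the control arm.

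No readable section makes randomisation, the pedometer or either link wait for the end of wear, for recalls two and three, or for the online social measures.

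**The concern.** Three of the measures that the protocol calls baseline are only started at the visit. If the end of the visit triggers randomisation, part of the baseline is recorded after allocation and after some material has gone out, contrary to Assessment Times. The material also differs by arm: controls have a health-information website, while LEAP participants have a step counter that the Moving More module uses for self-monitoring and goal setting.

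The trial is not powered for behavioural effects. Even so, the length-of-follow-up text under Randomisation says that the behavioural data will inform effect and sample size estimates for the definitive trial. The section on validity and responsiveness asks whether the monitor, the recall and the social measure can detect change. Both uses lean on a clean baseline, and a contaminated one cannot be repaired later.

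**Working it through.** No power or sample size figure bears on this point, so the check is a day count.

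**Inputs from the protocol.** The visit is day 0. Wear runs for 7 days from the visit (step 7). One of three recalls is done at the visit (step 7). Each recall covers the previous day's intake (Appendix A, Dietary intake). The control link goes out directly once the baseline assessment is over (step 10). The LEAP link follows confirmed pedometer receipt by 7 days (step 9).

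**Assumptions, not in the protocol.** Randomisation falls on day r = 0 or 1 if the visit is the trigger. Post takes p = 1 to 4 days. Confirmation of receipt adds c = 0 to 3 days.

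**Reading A: the trigger is the end of the visit**

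| Quantity | Formula | Result |
|---|---|---|
| Wear days overlapped by control link | 7 − r | 7 − 1 = 6 to 7 − 0 = 7 |
| Day pedometer arrives | r + p | 0 + 1 = 1 to 1 + 4 = 5 |
| Wear days overlapped by pedometer | 7 − (r + p) | 7 − 5 = 2 to 7 − 1 = 6 |
| Day LEAP web link is sent | r + p + c + 7 | 0 + 1 + 0 + 7 = 8 to 1 + 4 + 3 + 7 = 15 |
| Wear days overlapped by LEAP website | max(0, 7 − day sent) | 0 |

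The zero in the last row does not depend on the postal assumption: with r = p = c = 0 the link would go on day 7, when wear has ended.

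**Diet.** The first recall, on day 0, covers day −1 and precedes any link. If the recalls are on consecutive days, as in the examples in Appendix A, the second (day 1) covers day 0 and the third (day 2) covers day 1.

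- Control link on day 0: two of three intake days fall on or after the link day, but only one lies wholly after it.
- Control link on day 1: one of three falls on or after the link day.
- Recalls spaced further apart: up to two of three lie wholly after the link.

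The range is therefore 1 to 2 of 3, counted from the day the link is sent.

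**Social measures.** These are affected only if the participant uses the link after the visit. The documents do not settle when that happens.

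**Reading B: the trigger is completion of all baseline data.** Then r is at least 7, overlap with wear is at most 7 − 7 = 0 days in both arms, and all three recalls and the social measures are already in.

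**Which reading fits.** Two hours can cover a visit but not seven days of wear. Participant reimbursement counts two HAP assessments as about 4 hours, that is 4 / 2 = 2 hours each. The report that triggers randomisation comes from the visiting team member, whereas the device comes back by post and the remaining diet and social data arrive online. Reading A is the natural one for staff working through the steps in order.

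**Effect on estimates.** Let δ be the difference between arms (LEAP minus control) in the average early shift during the baseline window. A between-arm contrast of change scores moves by −δ. A baseline-adjusted contrast moves by −βδ, where β is the slope of follow-up on baseline. A contrast of follow-up values alone moves by 0. The protocol gives no basis for the size or sign of δ.

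**The case against.** A reader might infer that the protocol states outright that participants are randomised while baseline is still being collected. It does not. Assessment Times puts baseline first, the next section includes the behavioural measures in it, and step 8 waits for completion. Step 10 writes to people already allocated, so it follows step 8. Taken literally, this is Reading B and there is no overlap. Figure 2, which shows the administrative steps, is not available in the text reviewed and may settle the order. This stands, and it limits the finding to an undefined trigger whose natural reading conflicts with Assessment Times.

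Four stronger inferences also go too far.

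- **LEAP website.** It cannot reach participants inside the wear week; only the pedometer could.
- **Knowledge of allocation.** The protocol does not say that participants learn their arm before material arrives, and the Randomisation section describes them as blinded.
- **All behavioural baseline data.** The first recall is done at the visit. The social instruments might also be completed in that session, since Appendix A gives about 8 to 10 minutes for the psychological and social instruments together.
- **One-for-one loss of effect.** This holds only for raw change scores, and the protocol's Data Analysis section does not commit to them.

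Most of the research questions concern recruitment, retention, usage and completeness, which this barely touches. That limits the weight of the point but does not remove it, because the effect and sample size estimates and the sensitivity-to-change questions are also stated aims.

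**Conclusion.** The point holds in a limited form. Steps 7 to 10, followed in the way they most naturally read, randomise and release material while the 7-day wear, recalls two and three and possibly the online social measures are outstanding. Completion of baseline is not defined so as to prevent this.

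The exposure ranges in the working rest on the visit being the trigger and on the assumed posting and randomisation delays. They are days of exposure, not amounts of bias: the size and direction of any behavioural shift are unknown.

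What is at risk is baseline activity, diet and possibly social data, and any change score or baseline-adjusted estimate built on them. HAP tests completed at the visit and comparisons of follow-up values alone are unaffected.

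**What to change.** Define completion of baseline once, in Assessment Times and in Baseline and 2-month Follow-up Assessments, and use that definition in steps 8 and 10. Randomisation, posting of the pedometer and sending of any link should happen only after:

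- the 7-day wear has ended, and all three recalls and the online social measures have been submitted; or
- a prespecified cut-off has passed for participants with something outstanding (14 days after the visit is one possibility).

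Report losses between the visit and randomisation separately, so that they do not mix with retention by arm. Check that Figure 2 shows the same order.

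The cost is about 7 to 14 days' delay per participant, some tracking of devices and submissions by the administrator, and probably a few dropouts before randomisation. No extra visit is needed.

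The change does not remove the gap between the control and LEAP link dates. That gap is p + c + 7, or 1 + 0 + 7 = 8 to 4 + 3 + 7 = 14 days on the same assumptions, and it comes from the pedometer step.
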